### 8.7. Genetics

See [Appendix 8 \(Section 10.8.1.4\)](#) for information regarding genetic research for Japan.

### 8.7.1. Specified Genetics

A 4-mL blood PGx sample for DNA isolation will be collected into plastic K2-EDTA tubes, as defined in the [schedule of activities](#). DNA samples will be analyzed for the purpose of assessing the impact of allelic variants of drug metabolizing enzymes and transporters. Additionally, these samples may also be used for retrospective evaluation of additional genetic variants associated with variation in PK, biomarker response, or to explore AEs should these be observed. Samples will be retained for a period of up to 3 years after regulatory approval. In the event of DNA extraction failure, a replacement genetic blood sample may be requested from the participant.

See [Section 10.5](#) for additional information regarding genetic research. Details on processes for collection and shipment of these samples can be found in sponsor-identified study-specific central laboratory manual.

The PGx sample must be processed and shipped as indicated in the instructions provided to the investigator site, to maintain sample integrity. Any deviations from the PGx processing steps, including any actions taken, must be documented and reported to the sponsor. On a case-by-case basis, the sponsor may make a determination as to whether sample integrity has been compromised. Any sample deemed outside of established stability, or of questionable integrity, will be considered a protocol deviation.

As part of further understanding the biological response to study intervention, samples may be used for evaluation of other related genotyping as well as development and validation of bioanalytical methods.

### 8.7.2. Banked Biospecimens for Genetics

A 4-mL blood sample optimized for DNA isolation will be collected as local regulations and IRBs/Ecs allow.

Banked Biospecimens may be used for research related to the study intervention(s) and cancer. Genes and other analytes (eg, proteins, RNA, nondrug metabolites) may be studied using the banked samples.

See [Section 10.5](#) for additional information regarding genetic research. Details on processes for collection and shipment of these samples can be found in the laboratory manual.

## 8.8. Biomarkers

Biomarker samples will be collected from all relevant participants under consent

[figure not shown]

[REDACTED]  
[REDACTED] s well as hypothesis-free approaches by molecular profiling using baseline and/or progression tumor and/or plasma samples may also be performed.

Biospecimens collected for pharmacodynamic and other biomarker assessments may include peripheral blood, plasma, and tumor tissues, and may be used to analyze DNA, RNA, proteins, or metabolic biomarkers, for achieving planned biomarker objectives. Refer to the [SoA](#) for sample collection time points and the laboratory manual for sample processing and shipping. The following biospecimen types are planned to be collected in support of study objectives. Additional biospecimens collected over the course of participant disease management may be submitted for biomarker analyses. The biomarker sampling schedule may be modified based on emerging PK and/or PD data.

[REDACTED]  
A most recent archived tumor specimen from a recurrent tumor or distant metastasis other than bone is required and collected for all participants. If the archived tumor is not available or not sufficient, a de novo (fresh) baseline biopsy (any time before C1D1 treatment once all other general screening procedures have been completed and the participant is eligible for study treatment) is mandatory for all participants. In the event that the participant has bone disease only, or it poses a safety risk to the participant, in the opinion of the investigator and in consultation with the sponsor prior to enrollment, original diagnostic tumor tissue could be used for biomarker analyses. Consultation with the Sponsor prior to participant enrollment is required if this biopsy sample cannot be provided.

These tumor specimens will be used to analyze candidate nucleic acid and protein biomarkers for their ability to identify those participants who are most likely to benefit from treatment with the study intervention(s). [REDACTED]  
[REDACTED]

De novo (fresh) tumor paired biopsies obtained pre- and on-treatment are highly encouraged (optional) for participants in the dose escalation cohorts (Part 1A, Part 1B, [REDACTED]), however are mandatory for at least 5 participants in every part of 2A, 2B, [REDACTED]. Paired de novo tumor biopsies will be used to assess modulation of the levels of markers such as H3K23Ac, [REDACTED] as well as gene expression profiling changes after PF-07248144 [REDACTED] treatment.

[REDACTED]. Both baseline and on-treatment biopsies need to be collected if the participant has consented. On-treatment biopsy samples are to be collected on Cycle 1 Day 15 (+/- 2 days), 4 ± 2 hours post PF-07248144 dosing. If for safety reasons, the biopsy cannot be collected at this timepoint, it should be collected as soon as medically safe and feasible. In the event of any drug dose interruptions, biopsies should be taken 2 weeks after the patient resumes dosing. Paired tumor biopsies should preferably be taken from the same non-target lesion and from a lesion that has not been previously irradiated. Tumor tissue from cytologic sampling (eg, fine needle aspiration, including FFPE cell pellet material) or bone specimen, is not adequate and

should not be submitted. The EOT biopsy is optional but - encouraged. Additional information on tissue collection procedures can be found in the Laboratory Manual.

[REDACTED]  
Peripheral blood samples will be collected from all participants at the time points outlined in the SoA for measurement of the [REDACTED] correlate with doses and PK.

[REDACTED] Details regarding the collection, processing, storage and shipping of these samples will be provided in the Laboratory Manual.

In addition, blood samples optimized for [REDACTED] analyses will be collected from all participants at the time points outlined in the SoA. [REDACTED]

[REDACTED] d can be correlated with patient response.  
Examples of [REDACTED]

Additional analyses may be warranted based on emerging data.

### **8.9. Immunogenicity Assessments**

Immunogenicity assessments are not included in this study.

### **8.10. Health Economics**

Health economics/medical resource utilization and health economics parameters are not evaluated in this study.

## **9. STATISTICAL CONSIDERATIONS**

Detailed methodology for summary and statistical analyses of the data collected in this study is outlined here and further detailed in a SAP, which will be maintained by the sponsor.

The data will be summarized with respect to demographic and baseline characteristics, efficacy observations and measurements, safety observations and measurements, pharmacokinetic and biomarker measurements.

### **9.1. Statistical Hypotheses**

There will be no formal hypothesis testing in this study.

### **9.2. Sample Size Determination**

The total number of participants is estimated to be approximately 145 to 190.

### 9.2.1. Part 1 Dose Escalation

Approximately 70 participants will be enrolled in Part 1 including 25 to 30 participants in Part 1A, 6 to 9 participants in Part 1B, [REDACTED].

The actual number of participants enrolled will depend on the tolerability of PF-07248144 and the number of dose levels required to identify the MTD/RDE as monotherapy or in combination.

### 9.2.2. Part 2 Dose Expansion

**Part 2A:** Approximately 30 participants will be enrolled in Part 2A.

Assuming a non-informative prior (ie, Jeffrey's prior) if  $\geq 4$  out of 30 participants have tumor response, this would translate into a posterior probability (Beta Binomial) of more than 0.746 that the true response rate is not inferior to target response rate of 10%. Similarly, if  $\leq 2$  out of 30 participants have tumor response, this would translate into a posterior probability of more than 0.70 that the true response rate is not superior to the benchmark rate of 10%.

**Part 2B:** Approximately 30 participants will be enrolled in Part 2B.

Assuming a non-informative prior (ie, Jeffrey's prior) if  $\geq 6$  out of 30 participants have tumor response, this would translate into a posterior probability (Beta Binomial) of more than 0.786 that the true response rate is not inferior to target response rate of 15%. Similarly, if  $\leq 2$  out of 30 participants have tumor response, this would translate into a posterior probability of more than 0.70 that the true response rate is not superior to the benchmark rate of 10%.

[REDACTED]

[REDACTED]

[REDACTED]

### 9.3. Analysis Sets

1. Full analysis set.

The full analysis set includes all enrolled participants.

2. Safety analysis set.

The safety analysis set includes all enrolled participants who receive at least 1 dose of study intervention. Unless otherwise specified the safety analysis set will be the default analysis set used for all analyses.

3. Per protocol analysis set (evaluable for MTD).

The per protocol analysis set includes all enrolled participants who had at least 1 dose of study treatment and either experienced DLT or do not have major treatment deviations during the DLT observation period.

4. mITT Population.

The mITT is the analysis population that will follow the ITT principle and include participants receiving at least 1 dose of study medication with baseline assessment and at least 1 post baseline assessment, disease progression, or death before the first tumor assessment. The mITT population may be used for interim analysis and conference presentations when the study is still ongoing.

5. PK analysis sets.

The PK parameter analysis population is defined as all enrolled participants treated who do not have protocol deviations influencing PK assessment, and have sufficient information to estimate at least 1 of the PK parameters of interest.

The PK concentration population is defined as all enrolled participants who are treated and have at least 1 analyte concentration.

6. Response Evaluable Set.

The response evaluable population will include all participants who received at least 1 dose of study treatment and had baseline disease assessment and at least 1 post baseline disease assessment.

7. PD/Biomarker analysis set(s).

The PD/Biomarker analysis population is defined as all enrolled participants with at least 1 of the PD/Biomarkers evaluated at pre and/or post dose.

## 9.4. Statistical Analyses

The SAP will be developed and finalized before any analyses are performed and will describe the analyses and procedures for accounting for missing, unused, and spurious data. This section is a summary of the planned statistical analyses of the primary and secondary endpoints.

### 9.4.1. Maximum Tolerated Dose Determination

Determination of MTD will be performed using a Per protocol analysis set (evaluable for MTD).

### Bayesian adaptive approach:

The dose escalation in Part 1A, and dose finding in Part 1B [REDACTED] of the study will be guided by a Bayesian analysis of Cycle 1 DLT data for PF-07248144 as a monotherapy (Part 1A) or in combination (Part 1B, [REDACTED]). A traditional 2-parameter BLRM will be used to model the dose/DLT relationship of PF-07248144 monotherapy. A more complex BLRM model specifically designed for combinations will be used to model the dose/DLT relationship of PF-07248144 given in combination with fulvestrant, [REDACTED]  
[REDACTED]

Using DLT data at all tested dose levels and pre specified prior distribution of model parameters, the posterior distribution for probability of having a DLT will be calculated for all dose levels.

### Assessment of participant risk:

After each cohort of participants, the posterior distribution for the risk of DLT for new participants at different doses of interest for PF-07248144 will be evaluated. The posterior distributions will be summarized to provide the posterior probability that the risk of DLT lies within the following intervals:

|                  |              |
|------------------|--------------|
| Under-dosing:    | [0, 0.16]    |
| Targeted dosing: | [0.16, 0.33] |
| Overdosing:      | [0.33, 1]    |

### The EWOC principle:

Dosing decisions are guided by the escalation with overdose control principal. A dose may only be used for newly enrolled participants if the risk of excessive toxicity at that dose is less than 25%.

### Prior distributions:

Weakly informative prior distributions based on pre-clinical/expert opinion information will be chosen for the logistic parameters for prior distribution in Part 1A, see [Appendix 9 \(Section 10.9\)](#).

A **MAP approach** might be used to derive the prior distribution for model parameters used in Part 1B, [REDACTED] based on the data collected in Part 1A and DLT data collected in clinical studies for fulvestrant, [REDACTED].

The MAP prior for the logistic model parameters for this study is the conditional distribution of the parameters given the historical data. MAP priors are derived from hierarchical models, which take into account possible differences between the studies. A full description of the application of the MAP approach to derive the prior distributions of the model parameters is given in a Technical Supplement to [Appendix 9 \(Section 10.9\)](#).

In case of change of the dosing regimen, DLT data accumulated during the dose escalation with the original regimen may be used to form a prior for further BLRM analysis. Details about derivation of this prior using MAP approach is given in a Technical Supplement to [Appendix 9 \(Section 10.9\)](#).

**Starting dose:**

The starting dose of Part 1A is 8 mg QD. For this dose the prior risk of overdosing is 10.1%, which satisfies the EWOC criterion. A full assessment of the prior risk to participants is given in [Appendix 9 \(Section 10.9\)](#).

**Sensitivity Analysis:**

To mitigate the risk of dichotomizing and misclassifying DLTs, a sensitivity analysis that uses weighted DLT/AE data (in equivocal cases) into the BLRM model estimation will also be performed. If all the investigators and the sponsor agree on the equivocal DLT/AE data, the DLT weighting approach could be the primary dose escalation method. See [Appendix 9 \(Section 10.9\)](#) for more details.

**9.4.1.1. Stopping Criteria**

The trial will be stopped when the following criteria are met:

- At least 6 participants have been treated at the recommended MTD/RDE.
- The dose  $\tilde{d}$  satisfies one of the following conditions:
  - The probability of target toxicity at dose  $\tilde{d}$  exceeds 50%, ie,  $\Pr(0.16 \leq \pi_{\tilde{d}} < 0.33) \geq 50\%$ .
  - A minimum of 12 participants have been treated in the trial.
  - These stopping criteria are applicable to Part 1A, Part 1B, [REDACTED]

**9.4.2. Efficacy Analysis**

Response Evaluable Set will be used for all response related analyses including BOR, DOR, CBR, PFS, TTP and OS.

Tumor response will be presented in the form of participant data listings that include, but are not limited to tumor type, dose on Day 1, tumor response at each visit, clinical benefit response and best overall response. Proportion of participants responding to the treatment will be presented for each dose level.

For prostate cancer only, PSA and bone scan monitor, report and analysis should follow PCWG3 guidelines. Existing or new bone lesions as assessed by radionuclide bone scan will be described and documented.

PSA data will be presented in form of listings that include dose on Day 1, measurement, and % change from baseline at visit.

Part 1A, Part 1B, [REDACTED] Progression date, date of first response, last tumor assessment date, and date of last contact will be listed.

Part 2: The Kaplan-Meier methods will be used to analyze all time to event endpoints. Median PFS (if reached) will be calculated. DOR will be listed. Details of these endpoint analyses methods will be included in the SAP. Efficacy data of participants from Part 1A, Part 1B, [REDACTED] treated at the dose level selected for the corresponding expansion cohort and satisfying inclusion/exclusion criteria might be included in the analysis of efficacy endpoints of Part 2.

PFS is defined as the time from start date to date of first documentation of progression, or death due to any cause. Progression is defined as the appearance of local, regional or distant disease of the same type after complete response or progression of pre-existing lesions. It does not include second primary malignancies of unrelated types.

TTP - defined as the time from date of first dose to the date of the first documentation of PD.

OS is defined as the time from start date to date of death due to any cause.

CBR - defined as the proportion of patients with a best overall response (BOR) of CR, PR or SD lasting for 24 weeks.

The definition of each response category is provided in [Appendix 11 \(Section 10.11\)](#) (RECIST v1.1).

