1. INTRODUCTION

PF-07248144 is an orally available small-molecule inhibitor of human KAT6 histone acetyltransferases, KAT6A and KAT6B that is being investigated in participants with locally advanced or metastatic ER+ HER2- breast cancer, CRPC, or NSCLC who progress on or are intolerant to standard therapy.

This statistical analysis plan (SAP) provides the detailed methodology for summary and statistical analyses of the data collected in Study C4551001. This document may modify the plans outlined in the protocol; however, any major modifications of the primary endpoint definition or its analysis will also be reflected in a protocol amendment.

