### 3. ANALYSIS SETS (POPULATIONS FOR ANALYSIS)

Data for all participants will be assessed to determine if participants meet the criteria for inclusion in each analysis population.

| Population                                    | Description                                                                                                                                                                                                                                                                                                                                                                                                                                      |
|-----------------------------------------------|--------------------------------------------------------------------------------------------------------------------------------------------------------------------------------------------------------------------------------------------------------------------------------------------------------------------------------------------------------------------------------------------------------------------------------------------------|
| Full analysis set                             | The full analysis set includes all enrolled participants who will receive C1D1 dose. Unless otherwise specified the full analysis set will be the default analysis set used for all efficacy analyses.                                                                                                                                                                                                                                           |
| Safety analysis set.                          | The safety analysis set includes all enrolled participants who receive at least 1 dose of study intervention (including C1D-7). Unless otherwise specified the safety analysis set will be the default analysis set used for all safety analyses.                                                                                                                                                                                                |

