### 5.4. Efficacy Endpoint(s)

BOR, DOR, CBR, and PFS as assessed by investigator based on RECIST v1.1, are exploratory endpoints in Part 1 to evaluate the anti-tumor activity of PF-07248144. They, along with TTP, as assessed by investigator based on RECIST version 1.1, and Overall Survival are secondary endpoints in Part 2.

*Full Analysis Set will be used for all response related analyses including BOR, PFS, TTP, and OS. DOR will be analyzed only on responders.*

*Tumor response will be presented in the form of participant data listings that include, but are not limited to tumor type, dose on Day 1, tumor response at each visit, and best overall response. Proportion of participants responding to the treatment will be presented for each dose level.*

*For prostate cancer only, PSA and bone scan monitor, report and analysis should follow PCWG3 guidelines (see Protocol) Existing or new bone lesions as assessed by radionuclide bone scan will be described and documented.*

*PSA data will be presented in form of listings that include dose on Day 1, measurement, and % change from baseline at visit.*

*Part 1A, Part 1B, [REDACTED] Progression date, date of first response, last tumor assessment date, and date of last contact will be listed.*

*Part 2: The Kaplan-Meier method will be used to analyze all time to event endpoints. Median PFS (if reached) will be calculated. DOR will be listed. Efficacy data of participants from Part 1A, Part 1B, [REDACTED] treated at the dose level selected for the corresponding expansion cohort and satisfying inclusion/exclusion criteria might be included in the analysis of efficacy endpoints of Part 2.*

Part 1 and Part 2 data will be summarized separately, and may also be pooled together for analysis if deemed necessary, eg, to account for food effects subgroups. Specifically, the key tables in Part 2 include:

1. BOR is the best response recorded from the randomization until disease progression or death due to any cause. This is derived from the sequence of objective statuses. Objective statuses are not considered after objective progression is documented or after start of the first anticancer treatment post discontinuation of protocol treatment. BOR for each patient will be derived as one of the following categories.
  - Complete Response (CR): Two objective statuses of CR a minimum of 4 weeks apart documented before progression.

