  - Partial Response (PR) (applicable only to patients with measurable disease at baseline): Two objective statuses of PR or better (PR followed by PR or PR followed by CR) a minimum of 4 weeks apart documented before progression, but not qualifying as CR. Sequences of PR- Stable- PR are considered PRs as long as the 2 PR responses are observed at a minimum of 4 weeks apart.
  - Stable Disease (SD) (applicable only to patients with measurable disease at baseline): At least 1 objective status of stable disease or better documented at least 6 weeks after 'start date' and before progression but not qualifying as CR or PR. In this document, 'start date' for a patient is the date of first treatment (if study treatment start date is not available, date of enrollment is used) for non-randomized trials and the date of randomization for randomized trials.
  - Progressive Disease (PD): Progression documented within 17 weeks after 'start date' and not qualifying as CR, PR or SD.
  - Non-CR/non-PD (applicable only to patients with non-measurable disease at baseline): At least 1 non-CR/non-PD assessment (or better) documented at least 6 weeks after 'start date' and before first documentation of progression (and not qualifying for CR or PR).
  - 
  - Not Evaluable (NE): All other cases. Note that reasons for NE should be summarized and the following reasons could be used:
    - No adequate baseline assessment
    - No evidence of disease at baseline
    - No post-baseline assessments due to early death (ie, death prior to 6 weeks after 'start date')
    - No post-baseline assessments due to other reasons
    - All post-baseline assessments have overall response NE

- New anticancer therapy started before first post-baseline assessment
- SD of insufficient duration (< 6 weeks after 'start date' without further evaluable tumor assessments)
- PD too late (> 17 weeks after 'start date')
- Special and rare cases where BOR is NE due to both SD of insufficient duration ('too early') and late PD will be classified as 'SD of insufficient duration'.
- An objective status of PR, SD, or Non-CR/Non-PD cannot follow one of CR. SD can follow PR only in the rare case that tumor increases by less than 20% from the nadir, but enough that a previously documented 30% decrease from baseline no longer holds. If this occurs, the sequence PR-SD-PR is considered a confirmed PR. A sequence of PR – SD – SD – PD would be a best response of SD if the window for SD definition has been met.

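### Protocol 9.4.2 restricts response, PFS and OS to participants with a post-baseline tumour assessment, which drops unscanned early deaths and withdrawals and contradicts the SAP

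*Protocol*

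**What the plan says.** Protocol 9.4.2: "Response Evaluable Set will be used for all response related analyses including BOR, DOR, CBR, PFS, TTP and OS". Protocol 9.3 defines that set as participants who took at least one dose and "had baseline disease assessment and at least 1 post baseline disease assessment". Section 9.4.2 counts death from any cause as an event for both PFS and OS, and measures both from the start date. Under Table 3 the first scheduled on-study scan in Part 2 is at week 8, within 7 days either way.

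Protocol 9.3 also defines an mITT population that admits participants with "at least 1 post baseline assessment, disease progression, or death before the first tumor assessment", but 9.4.2 does not use it.

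SAP section 5.4 differs: "Full Analysis Set will be used for all response related analyses including BOR, PFS, TTP, and OS", with DOR analysed in responders. SAP section 3 makes the Full Analysis Set the default for efficacy, which covers CBR as well. Among the reasons for a Not Evaluable best response, SAP 5.4 lists "No post-baseline assessments due to early death", so such participants stay in the denominator. SAP Appendix 1, Table 2 counts a death within 17 weeks of the start date as a PFS event.

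The two documents define the Full Analysis Set differently. Protocol 9.3: "The full analysis set includes all enrolled participants". SAP section 3: "The full analysis set includes all enrolled participants who will receive C1D1 dose".

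**The concern.** Entry to the Response Evaluable Set depends on something that happens after treatment starts. A participant who dies without a post-baseline assessment has an OS event by definition but is absent from the OS analysis. Everyone analysed has therefore survived to a first assessment, while the clock still starts at the beginning of treatment. OS needs no scan, so inability to assess the tumour cannot justify the exclusion.

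For the response proportion and CBR, an unscanned participant cannot be a responder. Removing that participant shrinks the denominator and leaves the numerator alone, so the error is always in the drug's favour. There is no control arm to share it.

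Protocol 4.3.7 bases the final study RP2D partly on early signs of efficacy, and 9.2.2 reads response counts against 10% and 15%. A reader who follows the protocol and one who follows the SAP would report different denominators for the same endpoints.

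**Working it through.** **1. The two rules side by side, by type of participant with no post-baseline assessment**

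- *Death before any assessment.* Protocol: absent from every efficacy analysis. SAP: Not Evaluable in BOR, an event for PFS (if within 17 weeks) and for OS.
- *Alive, but withdrawn or lost before any assessment.* Protocol: absent. SAP: Not Evaluable in BOR, censored at the start date for PFS, censored at last contact for OS.

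Both types therefore inflate the response proportion and CBR. The bias in PFS and OS comes mainly from the unscanned deaths. TTP does not count death as an event and is little affected. DOR is confined to responders and is unaffected.

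**2. Reproducing the protocol's own figures (9.2.2)**

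Inputs: n = 30 and Jeffreys' prior, so with x responders the posterior is Beta(x + 0.5, n − x + 0.5).

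- Part 2A, 4/30: P(p ≥ 0.10) = 0.7455 (protocol 0.746).
- Part 2B, 6/30: P(p ≥ 0.15) = 0.7861 (protocol 0.786).
- 2/30: P(p ≤ 0.10) = 0.7091 (protocol: above 0.70).

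All three use the full 30 as the denominator, not a subset with scans.

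**3. The same responders with k participants unscanned**

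The documents give no value for k, so a range of 1 to 6 is assumed. The denominator becomes 30 − k.

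| k | n | 4 responders | P(p ≥ 10%) | 6 responders | P(p ≥ 15%) | 2 responders: P(p ≤ 10%) |
|---|---|---|---|---|---|---|
| 0 | 30 | 13.3% | 0.746 | 20.0% | 0.786 | 0.709 |
| 1 | 29 | 13.8% | 0.766 | 20.7% | 0.810 | 0.689 |
| 3 | 27 | 14.8% | 0.806 | 22.2% | 0.853 | 0.645 |
| 6 | 24 | 16.7% | 0.861 | 25.0% | 0.909 | 0.571 |

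One missing participant is enough to take the 2-responder figure below the stated 0.70.

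**4. PFS**

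Ignoring other censoring, if k of 30 die unscanned, then PFS in all treated = PFS in the evaluable set × (30 − k)/30. An assumed 6-month PFS of 50% in the evaluable set corresponds to 48.3% (k = 1), 45.0% (k = 3) or 40.0% (k = 6).

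**5. OS**

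Assume exponential survival with a median of 12 to 24 months, and week 8 = 56/30.4375 = 1.84 months. Deaths before week 8 = 1 − 0.5^(1.84/median):

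- median 12 months: 10.1%, about 3.0 of 30;
- median 24 months: 5.2%, about 1.6 of 30.

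If all of these were unscanned, the median in the remaining participants would be the true median plus 1.84 months (13.84 and 25.84). This is an upper figure for the model, because some of those who die early will have been imaged first.

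**The case against.** The strongest answer is that the problem has already been dealt with. SAP version 2 is dated 22 May 2023, after protocol Amendment 4 of 14 November 2022. Its introduction says "This document may modify the plans outlined in the protocol" and promises a protocol amendment only for major changes to the primary endpoint. A reader might infer from 9.4.2 that the trial will report the biased analysis; the documents do not support that, because the SAP's rule is the later one. What stands is that 9.4.2 fixes the population outright. It leaves only the details of the analysis methods to the SAP, and it remains the approved protocol text.

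Second, a reader might infer that everyone who deteriorates or stops before week 8 is excluded. That goes too far. Protocol 8.1.1 also calls for imaging when progression is suspected, and at withdrawal from treatment if none was done in the previous 6 weeks. Many early stoppers would therefore qualify, and early deaths after a first assessment stay in. Those lost are mainly deaths without imaging, withdrawals or losses without a scan, and very early stops where the baseline scan is still recent enough to waive another.

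Third, the stakes are limited. These endpoints are secondary in Part 2 and exploratory in Part 1, and there is no hypothesis test. The 10% and 15% rates illustrate the sample size, with no decision rule attached. A reader might suppose that PFS and OS are to be compared with historical data; the documents do not say so.

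Fourth, a large OS distortion should not be read into the plan. If 10% died unscanned before week 8 and true 6-month OS were 80%, the evaluable-set estimate would be 0.80/0.90 = 89%, but that front-loads the deaths. Under a constant hazard, 80% at 6 months implies survival of 0.80^(1.84/6) = 0.934 at week 8, giving 0.80/0.934 = 86%. Eligibility (ECOG 0 or 1, no visceral spread with short-term threat to life) also argues against heavy early mortality.

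**Conclusion.** The rule in protocol 9.4.2 is wrong as written. It conditions BOR, CBR, PFS, TTP and OS on a later assessment, biases the response proportion, PFS and OS upward, and contradicts the SAP.

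With 1 to 6 of 30 unscanned, the response proportion for 4 responders rises by about 0.5 to 3.3 percentage points, and the posterior probability against 10% rises by 0.02 to 0.12. The direction follows from the definitions; the size rests on the assumed k. The PFS and OS figures rest further on assumed survival rates and on how many early deaths escape imaging, so they are illustrations only.

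Because the later SAP already uses a better set and the endpoints are secondary or exploratory, this is a protocol-to-SAP correction. It does not threaten the primary safety objectives.

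**What to change.** Two changes to the protocol are needed together.

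1. In 9.4.2, replace the Response Evaluable Set with the Full Analysis Set for BOR and the response proportion, CBR, PFS, TTP and OS. State that a participant with no post-baseline assessment counts as a non-responder. Keep the Response Evaluable Set only for supportive response summaries. DOR stays in responders.
2. In 9.3, bring the Full Analysis Set into line with SAP section 3: enrolled and received the C1D1 dose. Changing 9.4.2 alone would bring never-dosed participants into the efficacy denominators and would still disagree with the SAP. The SAP set is also not quite all treated: a food-effect participant dosed only on Cycle 1 Day -7 is in the safety set but not in this one.

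The cost is an edit to two sections, with no new data and no change in sample size. The reported response proportion may be slightly lower.
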